#### Clinical data

2.5.3.

Participants will register in the NutriClock mobile application, specifically designed for this observational study by a multidisciplinary team, including computer engineers, nutritionists, physiologists, and psychologists (53). The NutriClock mobile application and backoffice were designed and developed to comply with ethical standards and the General Data Protection Regulation. The research team and authorized healthcare professionals will have access to the information that each participant introduces in the mobile application *via* the backoffice platform.

The clinical history information may be entered voluntarily by the participant when creating the account. Participants can also add or edit information in their profile after they are registered, at any time point. Healthcare professionals can also complete the information about the participant in the NutriClock backoffice. The information that will be collected includes sociodemographic data, diagnosed pathologies, and current medication.

#### Dietary intake assessments

2.5.4.

Dietary intake will be assessed using two methodologies: a 3-day food diary included in the NutriClock app (53) and a Food Frequency Questionnaire (FFQ). To ensure equal access and opportunity to participate in the research study, regardless of the socioeconomic level, availability of a smartphone, and/or ability to use it, participants can opt to complete the 3-day food diary in the traditional pen-and-paper format.

The participants will start filling out the 3-day food diary on the day of their visit to the research center to collect biological samples (Visit 2, Figure 1). All foods, including drinks, beverages, and dietary supplements consumed during the 3 days should be registered. Participants will also be required to register the meal time and type (breakfast, lunch, dinner or snack). Food portions will be estimated using either a photographic method (participants can take a picture of their meal through the mobile application), using the weight or volume, pre-determined household measures, and/or default mean portions where the participants cannot quantify a specific food item.

The conversion of food into energy and nutrients will be based on the Portuguese Food Composition Table (54), incorporated into the app and, if necessary, other food composition tables. In the app’s food diary section, participants can also upload pictures of the nutritional information/food labeling of the food items being consumed, if available. In the backoffice, it is possible to continuously adapt and complete the information on the Portuguese Food Composition Table by adding nutritional information for new food items or meals. The Portuguese Food Frequency Questionnaire (FFQ) is a validated semi-quantitative instrument that assesses dietary intake, reporting the previous 12 months. This tool will be used to collect information on the consumption of less frequently eaten foods and, therefore, minimize interferences with the day-to-day variation of food intake (55). The Portuguese FFQ includes a pre-determined list of 86 food items or groups, and nine frequency categories ranging from “Never or less < 1 per month” to “6+ per day” (56). Food consumption is quantified by multiplying the reported intake frequency by the food item or group average standard portion, and by a seasonal variation factor for items consumed only in a specific season. The conversion to nutrients will be supported by a compilation of databases on the nutritional food composition, including the Portuguese Food Composition Table (54).

The data collected with the FFQ will be mainly used to perform a global characterization of the participants’ dietary intake in the previous 12 months. The data collected using the 3-day food diary will be used to correlate dietary intake and circadian biomarkers.

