#### Biochemical assessments

2.5.2.

Peripheral blood samples (15–20 mL) will be collected from the participants at 08:00 a.m., after overnight fasting, and 04:30 p.m. on the same day, and aliquoted into EDTA tubes following safety standards, by certified healthcare professionals. Another blood sample (2.5 mL) will be collected from volunteers to PAXgene® Blood RNA Tubes (BD Biosciences), to obtain total RNA from whole blood.

For the total RNA from peripheral blood mononuclear cells (PBMC), blood samples will be diluted in 25 mL of Phosphate Buffered Saline (PBS) 1 × and added to 50 mL falcon tubes with 10 mL of Histopaque, density 1.077 g/mL. Samples will be centrifugated at 20^°^C to 22^°^Cand plasma will be immediately aliquoted and stored at −80^°^C. The interface bands, which contain the PBMC, will be aspirated into new 50 ml falcon tubes and washed with PBS 1 ×, followed by centrifugation at 21^°^C–25^°^C. Supernatants will be discarded and PBMC aliquots will be stored at −80^°^C until the analysis.

For the total RNA from whole blood, PAXgene® Blood RNA tubes will be centrifuged at 20 to 22°C and the supernatant removed. To the pellet, RNase-free water will be added and the samples vortexed until the pellet dissolution, followed by a centrifugation at 20^°^C to 22^°^C. After removal of the supernatant, a lysis buffer will be added, the sample vortexed and transferred to a 1.5 mL microcentrifuge tube where 40 μL of proteinase K will be added. After incubation, the sample will be transferred to a spin column of the Macherey Nagel RNA extraction kit, according to the manufacturer’s instructions. RNA concentration and purity will be determined using a spectrophotometer. Samples will be stored at −80^°^C until the analysis.

RNA samples will then be converted into cDNA and the mRNA levels of the clock genes (BMAL1, CLOCK, PER1-3, CRY1-2, CSNK1ε, REV-ERBα, REV-ERBβ, and DEC1) will be assessed using real-time quantitative reverse transcriptase polymerase chain reaction (qRT-PCR). Relative gene expression will be calculated according to the ΔCT method (51, 52).

Plasma levels of insulin, leptin, adiponectin, ghrelin, c-reactive protein, and interleukin-6 will be quantified using ELISA kits, according to the manufacturer’s instructions. Glucose will be assessed using the hexokinase method with a commercial kit.

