Circadian oscillations of gene expression also regulate whole-body metabolism (72). For example, Gaspar et al. showed that patients with obstructive sleep apnea, which is strongly related to obesity (73, 74), have different patterns of clock gene expression compared with healthy individuals (51), further highlighting the importance of assessing the circadian features in disease.

The importance of determining the circadian rhythm has been extensively reported; although it started more focused on pharmacological studies (40), this relevance has extended to nutrition. From this, the concept of chrononutrition emerged, mostly because peripheral circadian clocks are mainly synchronized by food intake (24, 31). Furthermore, the circadian clock also regulates nutrient challenges, through transcription factors that modulate the expression of genes with regulatory roles in nutrient pathways (37, 75) Therefore, there is the potential to improve metabolic homeostasis by coordinating behavioral changes with the body’s daily rhythm. The identification of genetic patterns and signatures in response to dietary intake may guide the advance of new therapeutic approaches.

Designing dietary interventions that account for the quality, quantity and timing of food intake could be an approach to modulate the circadian rhythm and clock-controlled genes and optimize the synchronization of central and peripheral clocks, with a positive impact on overall metabolism. Therefore, the characterization of circadian and dietary makers is a critical first step to underpin therapeutic strategies and to support the adjustment of chrononutritional approaches for the management of chronic diseases such as obesity. In the present study, caloric intake, macronutrients (proteins, carbohydrates, and lipids), and meal times (time of the first meal of the day, time of last meal of the day and overnight fasting period) will be evaluated, in order to assess the impact of dietary intake (timing and nutrients) on circadian rhythm markers.

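### The 3-day food diary starts on the sampling day, so it misses the last meal and overnight fast before the 08:00 draw and cannot support an effect of intake on the biomarkers

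*Protocol article*

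**What the plan says.** Under Dietary intake assessments (2.5.4), the diary is tied to Visit 2: "The participants will start filling out the 3-day food diary on the day of their visit to the research center to collect biological samples". It is meant to be complete from then on: "All foods, including drinks, beverages, and dietary supplements consumed during the 3 days should be registered". The same section gives the two dietary instruments different jobs. For the diary: "The data collected using the 3-day food diary will be used to correlate dietary intake and circadian biomarkers". For the food frequency questionnaire: "The data collected with the FFQ will be mainly used to perform a global characterization of the participants’ dietary intake in the previous 12 months".

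Under Biochemical assessments (2.5.2), the blood samples "will be collected from the participants at 08:00 a.m., after overnight fasting, and 04:30 p.m. on the same day". Clock-gene expression and the metabolic markers come from this sampling.

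The Discussion names the meal-timing variables ("time of the first meal of the day, time of last meal of the day and overnight fasting period") and says that intake is evaluated "in order to assess the impact of dietary intake (timing and nutrients) on circadian rhythm markers". So diet is the exposure and the circadian markers are the outcome.

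**The concern.** When intake is meant to explain a biomarker, the intake record should cover the time before the sample. Here it opens on the day of the sample. The protocol's own rationale makes the missing hours relevant. The Introduction describes peripheral clocks as set by cycles of feeding and fasting, and says that nutrients act quickly on clock genes, Per2 and Rev-erbα in particular. PER2 and REV-ERBα are among the genes measured, and the Discussion expects them to differ between groups.

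Two things are at stake. First, a correlation between the markers and meals eaten afterwards cannot be read as an effect of those meals. Second, the sampling day is not an ordinary day for first-meal time, because a fast until 08:00 is required.

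**Working it through.** The protocol states no figure for this point, so there is none to reproduce. The check places the diary window against the two draws.

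**Inputs**
- Diary: 3 days, the first being the sampling day, called day 0 here (2.5.4). That the days are consecutive is an assumption.
- Draws on day 0: "at 08:00 a.m., after overnight fasting, and 04:30 p.m. on the same day" (2.5.2).
- Timing variables: first meal, last meal, overnight fast (Discussion).
- Assumption for counting meals: 3 main meals a day, with day-0 breakfast after 08:00 and lunch before 16:30.

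**Step 1: hours.** The window from midnight of day 0 is 3 × 24 = 72 h.

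| Part of the window | Hours | Share |
|---|---|---|
| Before 08:00 on day 0 (required fast, no meals) | 8.0 | 8.0/72 = 11% |
| Between the draws | 16.5 − 8.0 = 8.5 | 8.5/72 = 12% |
| After 16:30 on day 0 | 72 − 16.5 = 55.5 | 55.5/72 = 77% |

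**Step 2: main meals.** There are 3 × 3 = 9.
- Before the 08:00 sample: 0 of 9.
- Before the 16:30 sample: 2 of 9 (day-0 breakfast and lunch).
- After the 16:30 sample: 7 of 9 = 78%.

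**Step 3: overnight fasts.** Days 0, 1 and 2 give two complete fasts, the nights 0–1 and 1–2. Both follow both samples. The fast into the 08:00 draw begins with the last meal of the evening before day 0, which lies outside the diary.

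**Step 4: which timing values the visit constrains.** The diary yields 3 first-meal times, 3 last-meal times and 2 fasts, 8 values in all. The fasting draw directly constrains one, the day-0 first meal. That is 1 of 3 first-meal times, or 1 of 8 timing values (12.5%).

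**Step 5: effect on a group difference in first-meal time.** Let the true difference be 60 minutes and let d be the difference seen on day 0. If the three days are averaged, the recorded difference is (d + 60 + 60)/3.
- Everyone eats at the same clock time on day 0 (d = 0): 120/3 = 40 minutes.
- The draw constrains nobody (d = 60): 180/3 = 60 minutes.
- Partial constraint falls between 40 and 60 minutes.

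**The case against.** The strongest reply is that the article plans only correlations and states its objective as a relation between chronotype, phenotype and dietary patterns. A short diary next to a blood draw can stand in for usual intake, and for a stable habit the recording date matters little. This stands in part: a diary starting on day 0 can still proxy usual intake. But the article does not give it that role. It assigns the 12-month picture to the food frequency questionnaire and uses the language of impact for intake and timing. The limitations in the Discussion mention self-report bias and the two sampling times, but not diary timing.

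Other parts of the reply stand, and rule out stronger readings that a reader might infer:
- **That all recorded intake follows the biomarkers.** This is true only for the 08:00 sample. Meals between the draws precede the 16:30 sample.
- **That a third of all meal-timing data is an artefact of the visit.** One third applies to first-meal time alone. Last-meal time and overnight fast are not directly attenuated in this way.
- **That 20 of every 60 minutes are lost.** That is the worst end of the range. If both groups usually eat well after 08:00, the draw need not attenuate anything. The article does not say whether day 0 is averaged in, and it may leave that to a fuller document.

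Moving the diary also has a price. Recording before the draw could change eating before the markers are measured, whereas a diary that starts at the draw cannot affect the 08:00 sample. The evening before a fasting draw is also partly shaped by the visit.

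**Conclusion.** The point holds in a limited form. The diary assigned to the diet-biomarker correlation contains no meal before the 08:00 sample. Before the 16:30 sample it contains only the meals between the draws, about 2 of 9 main meals under the stated assumption. The last meal and overnight fast leading into the fasting sample are never recorded. As designed, the data can support an association with usual intake, but not the stated impact of intake and timing on the markers.

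For first-meal time, one value of three is constrained by the visit, and a true 60-minute group difference would be recorded as 40 to 60 minutes if day 0 is averaged in.

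This rests on consecutive diary days and on the text of 2.5.2 and 2.5.4. Figure 1 is not shown, but the order of diary and draws does not depend on it. A reader might go further and call the diary-biomarker analysis worthless. The documents do not support that, because the diary keeps some value as a proxy for habit.

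**What to change.** **Preferred.** Run the diary over the 3 days ending the evening before Visit 2, and add a short note of the time and content of meals eaten between the two draws. Derive usual first-meal time, last-meal time and overnight fast from the pre-visit days. Treat the fast into the draw as a separate variable, because the visit requires it.

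**If the diary start is kept.**
- Record the time and content of the last meal before the 08:00 draw.
- Leave the day-0 first meal out of habitual timing, or run a sensitivity analysis without day 0.
- Describe the results as associations with usual intake, and drop the language of impact.

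**Cost.** The preferred change means a new diary start date, new reminder timing in the app and a brief visit-day note, with no extra visit or assay. Visits 1 and 2 must be at least 3 days apart; the text gives no interval between them, so this needs checking against the visit schedule. Recording before sampling may slightly alter eating. The fallback costs one added question and a change of wording.

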#### Questionnaires

2.5.5.

To complete the participant’s characterization and data, a set of validated questionnaires and instruments will be used.

The Pittsburgh Sleep Quality Index (PSQI) is a 19-items (plus 5 additional items, in case the responder has a roommate or bed partner, that do not contribute to the total score) self-reported questionnaire, designed to subjectively assess global sleep quality based on the participant’s retrospective evaluation (considers the usual sleep habits over the past one-month period). The items of the PSQI are divided into seven components, namely, subjective sleep quality, sleep latency, sleep duration, habitual sleep efficiency, sleep disturbances, use of sleeping medication, and daytime dysfunction, each weighted equally on a scale from 0 to 3. The global PSQI score ranges from 0 to 21, corresponding to the sum of the seven components. A global PSQI score greater than 5 indicates major difficulties in at least two components or moderate difficulties in more than three components (57, 58). This instrument has been validated for the Portuguese population (59).

The Munich Chronotype Questionnaire (MCTQ) was developed by Roenneberg and colleagues to assess the circadian phase of entrainment, which is considered a quantifiable biological phenotype (41, 60). The questions aim to evaluate sleep behavior on workdays and work-free days, separately, since this distinction is essential to determine the participant’s chronotype. The chronotype resultant from the MCTQ is expressed in local time and it is based on the Mid-Sleep time in Free days (MSF) after correction for potential compensatory sleep (MSF_sc_) (60). The midpoint of sleep has been considered one of the most accurate behavioral markers to determine the circadian phase (60, 61). However, to account for the sleep debt as a cofounder, it is necessary to calculate the average sleep duration of the entire week and correct MSF by subtracting half of the oversleep. According to the results of the MCTQ database, Roenneberg and colleagues identified seven groups based on MSF_sc_, namely, extremely early, moderately early, slightly early, intermediate, slightly late, moderately late and extremely late (60). This instrument has already been validated for the Portuguese population (62).

### Statistical analysis

2.6.

Statistical analysis will be performed using the IBM SPSS Statistics software version 28.0.1. (IBM Corp., Warrington, United Kingdom) and GraphPad Prism version 8 (GraphPad Software, Inc.; San Diego, United States). Continuous variables will be presented as the mean ± standard deviation (SD), median, and interquartile range [Q1–Q3]. Categorical variables will be presented in frequency and percentage. The normality of continuous variables will be tested using the Shapiro–Wilk test if *n* < 50 or the Kolmogorov–Smirnov test if *n* ≥ 50. Parametric tests (Independent Sample *t*-test) will be used to compare the differences between the study and the control groups if the data has a normal distribution, otherwise, non-parametric tests (Mann–Whitney *U*-tests) will be performed. According to the normality or non-normality of data distribution, Spearman’s rank-order correlation (ρ) or Pearson’s correlation coefficient (r) will be performed to calculate and assess the strength of correlations between the study variables. Statistical significance will be set at *p* < 0.05.

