### Participant selection

2.2.

Participants will be recruited from healthcare centers in Leiria, Portugal. The study will also be disseminated through social networks and institutional emails, in an attempt to reach more participants.

The eligibility of the participants will be assessed on the first visit by the assessment of inclusion and exclusion criteria after the potential participants signed the informed consent. The observational study will be conducted on adults and recruitment will be gender-independent. Obesity will be defined according to the criteria of the World Health Organization (1). The detailed participant inclusion and exclusion criteria are listed in Table 1.

**Table 1 tab1:** Inclusion and exclusion criteria for the participants in both study groups.

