**Inclusion criteria**
Adults aged ≥ 18 and ≤ 75 years. BMI ≥ 30 kg/m^2^ (study group). BMI ≥ 18.5 and < 25.0 kg/m^2^ (control group).

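### The analysis described uses only unadjusted two-sample tests and simple correlations for a non-randomised comparison; age and sex should enter the main models, and correlations should also be shown within or adjusted for group

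*Protocol article*

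**What the plan says.** Section 2.6, Statistical analysis, describes these inferential methods: independent-samples t-tests that "will be used to compare the differences between the study and the control groups if the data has a normal distribution", Mann–Whitney tests otherwise, and Pearson or Spearman coefficients that "will be performed to calculate and assess the strength of correlations between the study variables". The significance level is 0.05. No covariate, regression model, partial correlation or within-group correlation is mentioned, and the section does not say whether correlations are computed over both groups together or within each.

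On design, Table 1 admits "Adults aged ≥ 18 and ≤ 75 years" to both groups. The study group has a BMI of at least 30 and the control group a BMI from 18.5 to below 25, so nobody between 25 and 30 is included. Section 2.2 recruits through healthcare centres and adds: "The study will also be disseminated through social networks and institutional emails". On sex it says: "The observational study will be conducted on adults and recruitment will be gender-independent". No matching, stratification or restriction on age or sex is described beyond the common age limits.

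Section 2.5.3 says: "The information that will be collected includes sociodemographic data, diagnosed pathologies, and current medication". These data are given no role in the analysis. Section 2.5.4 assigns the 3-day food diary to correlations between diet and circadian biomarkers, and the Discussion states the purpose of these data as judging the impact of diet on circadian rhythm markers.

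**The concern.** Two separate mechanisms are involved.

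The first is ordinary confounding. Age and sex are plausible determinants of chronotype, body composition, adipokines and gene expression. In a non-randomised comparison over a 57-year age span nothing in the design holds them equal, and the tests described cannot remove an imbalance if one arises. Recruiting without regard to sex does not balance sex between the groups. A difference in chronotype or clock genes attributed to obesity could then be partly a difference in age or sex.

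The second is structural. The sample consists of two groups separated on BMI. If a dietary variable and a clock gene both differ between them, a correlation over the combined sample is non-zero even when the two are unrelated inside each group. Such a coefficient partly restates the case–control contrast, whereas the Discussion wants to read it as an effect of diet on circadian markers.

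**Working it through.** **1. Sample size used.** The article's formula with p0 = 0.18 and p1 = 0.55 gives (0.1476 + 0.2475) × (1.96 + 0.84)² / 0.37² = 0.3951 × 7.84 / 0.1369 = 22.63, so 23 per group and 46 in total. This reproduces the stated figure. The enrolled minimum is 32 per group. Section 2.3 expects attrition at visits 2 and 3, and section 2.5.4 places the biological samples at visit 2, so 23 is the relevant planned number for the biomarkers. Results at 32 are shown for comparison.

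**2. Group comparison with no true group effect.** Assumptions, because the documents give no figures: the groups differ in mean age by D standard deviations, the outcome correlates r with age within groups, and group itself has no effect. The spurious standardised difference is r × D. The rejection rate of the two-sided 5% t-test follows from the noncentral t distribution with noncentrality r × D × √(n/2) and 2n − 2 degrees of freedom. Example: r = 0.4, D = 1 and n = 23 give 0.4 × √11.5 = 1.36 on 44 degrees of freedom, a rejection rate of 26%.

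| r | D (SD) | spurious difference (SD) | 23 per group | 32 per group |
|---|---|---|---|---|
| any | 0 | 0 | 5% | 5% |
| 0.2 | 0.5 | 0.10 | 6% | 7% |
| 0.2 | 1.0 | 0.20 | 10% | 12% |
| 0.3 | 0.5 | 0.15 | 8% | 9% |
| 0.3 | 1.0 | 0.30 | 17% | 22% |
| 0.4 | 0.5 | 0.20 | 10% | 12% |
| 0.4 | 1.0 | 0.40 | 26% | 35% |

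A simulation with 20,000 replicates per cell agrees: for r = 0.3 and D = 1 it gives 16.6% at 23 per group and 22.1% at 32. With age in the model, every simulated scenario returned to between 4.7% and 5.4%.

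**3. Correlation over both groups, none within either.** Assumption: the two variables differ between equal-sized groups by d1 and d2 within-group standard deviations. The pooled correlation is (d1 × d2 / 4) / √[(1 + d1²/4)(1 + d2²/4)]. The chance of significance comes from Fisher's z, atanh(r) × √(N − 3) against 1.96. Example: d1 = d2 = 1 gives 0.25 / 1.25 = 0.20; at N = 46, 0.203 × √43 = 1.33, or 26%.

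| d1, d2 (SD) | pooled r | N = 46 | N = 64 |
|---|---|---|---|
| 0.5, 0.5 | 0.06 | 7% | 8% |
| 1, 1 | 0.20 | 26% | 35% |
| 2, 1 | 0.32 | 57% | 72% |

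Simulation gives 6.6% and 7.8% for the first row and 27.1% and 36.4% for the second. Partialling on group brings the simulated rates back to about 5%.

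**The case against.** Five points can be made for the plan.

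- **The aim is partly descriptive.** The article sets out to characterise and compare, and an unadjusted contrast answers that question validly. This stands, and it is why the unadjusted test should be kept. It does not cover the language about the impact of diet.
- **Some confounding is handled by design.** Shift workers, recent time-zone travellers, people with diagnosed sleep disorders and regular users of several relevant drugs are excluded. Chronotype is corrected for sleep debt, and blood is drawn at fixed times. This stands, but none of it deals with age or sex.
- **This is a condensed article.** Adjusted analyses may exist in a fuller plan. The statement here is therefore limited to the analyses described. Those are named explicitly, so this is a remark on a stated choice and not on an omission.
- **Adjusting correlations for group changes the question.** It removes the between-group contrast in adiposity that the design creates, and relation to phenotype is an objective. This stands: adjusted coefficients belong beside pooled ones and should not simply replace them.
- **No imbalance is documented.** This also stands. With none, the t-test keeps its 5% level.

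A reader might also infer two things that the text does not support. One is that cases come from clinics and controls from social networks and email, so that the groups are bound to differ in age and sex; section 2.2 assigns no route to either group. The other is that the normality rule's branch for n ≥ 50 proves that pooled analysis is intended because groups number 32. The total of 64 is a stated minimum and recruitment may be extended, so a group could reach 50, and a generic normality rule does not show how correlations will be run.

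**Conclusion.** The point holds in conditional form. The analyses described do not protect the group comparison against an age or sex imbalance. Nor do they protect the diet–biomarker correlations against the two-group structure if the groups are pooled.

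Under the assumed age gaps and age–outcome correlations, the 5% test rejects about 6% to 26% of the time at 23 evaluable per group (7% to 35% at 32). For pooled correlations the range runs from 7% to 57% (8% to 72%) as the separations grow from 0.5 SD in both variables to 2 SD and 1 SD. The upper values need large separations, and nothing in the documents shows that diet and circadian markers differ that much; the low end should be quoted with the high end.

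It would be too strong to say that the results will be spurious, or that the groups are known to be unbalanced. What can be said is that the described analysis could not tell these explanations apart, and that an inexpensive change would let it do so for age, sex and group.

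**What to change.** In section 2.6:

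1. Make the main group comparison a linear regression of each main outcome, log-transformed where skewed, on group, age and sex. Keep the t-test or Mann–Whitney test as a descriptive result.
2. State whether correlations are computed over both groups or within each. Beside any pooled coefficient, report within-group coefficients or partial (rank) correlations adjusted for group, age and sex. Base statements about diet and circadian markers on the adjusted ones.
3. Confirm that age and sex are recorded for every participant. Age is needed for eligibility, and sex would fall under the sociodemographic data, but section 2.5.3 makes some profile entries voluntary.

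**Cost.** The regression uses two more degrees of freedom than the t-test (42 instead of 44 at 23 per group), and the partial correlation three more than the simple one (41 instead of 44). If the groups do differ in age, adjustment also widens the interval somewhat: with a 1 SD gap, group and age share 0.25 / 1.25 = 20% of their variance, so the variance of the group estimate rises by a factor of 1 / 0.8 = 1.25 before any gain from explaining the outcome by age. The group-adjusted correlations set aside the between-group contrast, which is why the pooled ones may stay alongside.

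Frequency-matching controls on sex and broad age band would help but is optional; the fix does not depend on it.
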